# Study Assessment Table

| Visit🡪 | Screening | Visit  Enrolment | 1^st^ Follow up | 2^nd^ Follow up | 3^rd^ Follow up |
| --- | --- | --- | --- | --- | --- |
| Study Procedure | (Day -2 to Day 0) | Day 0 | Day 5^th^ (+1) | Day 15^th^ (+2) | Day 30^th^ (+2) |
| ICF | X | X |  |  |  |
| I/E Criteria | X | X |  |  |  |
| Demographics | X |  |  |  |  |
| Vitals and Physical Examination |  | X | X | X | X |
| Medical History | X |  |  |  |  |
| Questionnaire |  | X | X | X | X |
| Investigations |  | X*^#^ | X^#^ |  | X* |
| Bottle Dispensing |  | X |  | X |  |
| IP / Placebo Accountability |  |  | X | X | X |
| AE/SAE | X | X | X | X | X |

Investigations –

*TH1, TH2, Th17, IL6, NK Cells and CD markers; Immunoglobulin IGG (Serum); Immunoglobulin IGM (Serum); Liver Function Test and Kidney Function Test

Around 2 ml of blood will be stored for additional biomarker in Immunology and Virology.

^#^COVID-19 RT PCR (quantitative): This test will be conducted on day 3±1 day on 5 subjects of each group. Same group: Sr. Ferritin, CRP and D-Dimer will be done on day 0 and 5.

Clinical investigations like chest X ray, ECG will be done as per physician’s discretion. Vitals and Physical Examination: If physician is not in a position to perform, s/he will extrapolate the data from the available information.

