# Study Design

Overview of the Study Design

- This is a randomized, 2-arm, parallel group, double-blind, 1:1 ratio, controlled, exploratory trial with a study period of 30 days from the of enrolment.
- A total of up-to 75 known COVID-19 positive (with positive RT-PCR) patients will be enrolled in the study.
- All the patients enrolled in the study will get the Investigational Product (IP-1 and IP-2), or 2 capsule of Placebo in similar sized and colored bottles, two times daily for the 1^st^ 15 days. From 16^th^ day onwards patients will get one capsule twice daily i.e. IP-2 or capsule placebo up to day 30.
- Patients will undergo laboratory investigations upon enrolment and on last visit. RTPCR for COVID will be done on day 5 (+ 1 day).
- Patients and doctors treating will not be knowing what the participating subject has received. Subjects will be given coded bottles, containing dose for 30 days.
- No medicine which his/her physician is giving will be stopped. No modifications shall be suggested in their diet and daily routine physical activities.
- Thus, patients enrolled in the study will get the IP / Placebo in addition to the standard of care which they were already receiving at the time of enrolment.
- Half of patients will be getting Cap. IP and half will be getting Cap. Placebo throughout the study duration of 1 month.

Study period for enrolled patients will be 30 days:

- Enrollment (day 0): After Informed Consent Process, Demographics and other information for CRF will be recorded. Investigations: COVID 19 RTPCR, Lymphocyte subset analysis (TH1, TH2, Th17, IL6, NK Cells and CD markers); Immunoglobulin IGG (Serum); Immunoglobulin IGM (Serum); Liver Function Test and Kidney Function Test will be done. Cap. bottle will be given to the patients with the dose lasting for 30 days.
- Day 3±1: COVID-19 RT PCR (quantitative) test will also be conducted on day 3 (±1) on 5 subjects of each group
- Follow-up 1: Day (5±1): COVID-19 RT PCR (quantitative) test will be conducted for all subjects on Day (5±1). CRF will be filled for knowing the overall status.
- Follow up 2 (15^th^ day+ 2 days): This follow up will be clinical/telephonic. CRF will be filled for knowing the overall status.

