- Follow up 3 (30^th^ day+ 2 days): Patients will be followed up at day 30. This visit will be done telephonically. Patient will not visit site but blood investigations shall be carried out. Investigations will be done outside the site, considering that the site is COVID specific hospital. The investigations are; Lymphocyte subset analysis (TH1, TH2, Th17, IL6, NK Cells and CD markers); Immunoglobulin IGG (Serum); Immunoglobulin IGM (Serum); Liver Function Test and Kidney Function Test will be done. All the unused IP will be collected.
- Sponsor will provide 10 codes (5 from each, IP and placebo, not mentioning which is placebo and IP). These will get Sr. Ferritin, CRP and D- Dimer done for same patients on day 0.

Every time subject coming to the scheduled follow-up should be asked to bring the remaining capsules with the bottle.

Flow chart

Screening

(I/E Criteria, ICF reading)

Enrollment (Day 0) Randomization

IP Arm Placebo Arm (30 patients in each arm)

(Consenting, Clinical Exam, Investigations, QOL, IP / Placebo Dispense)

COVID-19 RT PCR (quantitative) test on day 3 (±1) for 5 subjects of each group

1^st^ Follow-up: Day (5±1)

COVID-19 RT PCR (quantitative)

2^nd^ Follow-Up: Day (15+2)

[Clinical/telephonic]

3^rd^ Follow-Up: Day (30+2)

[Tele follow-up Blood Investigations at lab]

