# **Methods and Procedures**

Patients attending COVID treatment center (YCM Hospital, Pimpri, Pune, India) of the investigators will be screened for their participation in the study. Patients should be COVID-19 positive, diagnosed recently. No discretion for enrollment will be made based on gender, color, religion and cast. Information about the study will be shared with the patients and their eligibility will be checked during screening. Those fulfilling this requirement and who are willing to participate will be given informed consent document and patient information sheet for reading. Adequate time will be given for reading the same and the same will be explained verbally. All questions will be answered to the patients’ satisfaction. Patient will be considered as enrolled only after consenting procedure is done.

Patients will be counseled about administration of IP (dose, timing, method etc.). In case of SAE / other event which necessitates to break the blind, it will be broken. Appropriate treatment will be provided and the IP might be discontinued if investigator thinks this in the best health interest of the participant.

Follow-Up:

After enrollment (Day 0), there will be one clinical and the next two: either telephonic or clinical follow-ups: first follow-up visit at day 5 (+1 day), second follow-up visit at day 15 (+2 days) and third follow-up visit at day 30 (+2 days).

Patients will need to make sure, there is no gap in consuming the IP.

Patients can call the study coordinator anytime for the queries if any.

Unscheduled Visits:

Patients will continue to visit his/her physician at the site for medical care with prior appointments for routine and regular check-ups. Study coordinator will try and combine their study follow-up visit with their regular visit at the site. Patients should, as far as possible, visit the site in case of medical emergencies.

Study Design:

This is a two arm, double blind, randomized, controlled, prospective study to determine safety and efficacy of Cap. IP in COVID-19 positive patients.

After enrollment, they will get the IP / Placebo in addition to their regular treatment they might be receiving for their condition. (2 capsules twice a day for prior 15 days and 1 capsule twice a day from day 16)

A total of 60 patients (Can be extendable to 150) will be enrolled in the study in different groups. The reason behind this sample size that, we can apply paired t test with adequate power for an exploratory study.

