# Study Assessments:

Participants will have a minimum of two follow-ups. Clinical assessment will be done; vitals will be noted, questionnaire will be filled-in and blood will be collected for various parameters.

Study Conduct:

Patients screened, eligible and willing will be enrolled in the study and IP will be dispensed. During screening, inclusion-exclusion criteria will be applied. Those fulfilling the criteria will be given detailed information about the study. Of those who are willing to participate will be asked to sign the informed consent form. Study coordinator with the principal or co-principal investigator will participate in the consent process.

Day of consenting will be done on the day of screening. After signing the consent form, on enrollment day, physical examinations will be done; blood will be withdrawn for investigations, case record form will be filled and IP will be dispensed. A copy of duly signed informed consent form will be given to them.

Follow-up Visit 1 [5^th^ day (+ 1) of the day of enrollment]: Questions will be asked about adherence, missed doses if any and adverse events if any. NP swab will be collected for RT-PCR of COVID-19

Follow-up Visit 2 [15^th^ day (+ 2) of the day of enrollment]: All the procedures for this visit will be the same as that of Visit 1, except that swab will not be collected for RT PCR.

Follow-up Visit 3 [30^th^ day (+ 2) of the day of enrollment]: All the procedures for this visit will be the same as that of Visit 2, and in addition, blood will be drawn for various markers.

Discontinued Patients:

Patients will be withdrawn/dropped from the study if they violate the protocol e.g. by participating in other study, by not taking the IP, not coming to the hospital for follow-up etc. Patients developing any serious disease, patients wanting to withdraw will also be withdrawn from the study.

Patients who have not turned for clinical follow-up will be called telephonically up to three times after the window period is over. During consenting they will be asked if it is alright with them.

However, as it is a ‘intent-to-treat’ (ITT) study design, data collected of such patients, till they are dropped out/withdrawn from the study will be included in the analysis.

Patients will be insisted to visit during the window-period. Those who miss this will still be continued into the study. On case-to-case basis, protocol waivers will be granted by the co-PI and/or the PI.

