- Efficacy of the herbal extracts in COVID 19 positive patients (in declining viral load: time-point: 5 days and early recovery)

Secondary Outcomes:

- - Efficacy of the herbal extracts as an immune-modulator - TH1, TH2, Th17, IL6, NK Cells and CD markers; Immunoglobulin IGG (Serum); Immunoglobulin IGM (Serum): at 30 days.
  - Efficacy of the investigational product in reducing sequela of the disease
  - Safety analysis (Liver Function Test and Kidney Function Test) including serious allergic reaction of: rash, itching/swelling, severe dizziness, trouble breathing.

1. Details about the Investigator*

Name

Address

Telephone number

Profession (specialty)

Date of reporting the event to Ethics Committee:

Signature of the Investigator

Information marked ‘*’ must be provided.

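### A table footnote has physicians extrapolate vitals and examinations they could not perform, at visits that may be by telephone, with no stated flag on such values

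*Protocol*

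**What the plan says.** The Study Assessment Table marks vitals and physical examination at enrolment and at all three follow-ups (days 5, 15 and 30). Its footnote adds: "If physician is not in a position to perform, s/he will extrapolate the data from the available information". Study Assessments repeats the requirement in general terms: "Clinical assessment will be done; vitals will be noted, questionnaire will be filled-in and blood will be collected for various parameters".

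The mode of the later visits is described in two places. Study Design says of day 15: "This follow up will be clinical/telephonic". Of day 30 it says: "This visit will be done telephonically. Patient will not visit site but blood investigations shall be carried out". Methods and Procedures says that after enrolment "there will be one clinical and the next two: either telephonic or clinical follow-ups", which makes day 5 the clinical visit and leaves both later visits open.

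The outcomes, listed within the Study Treatment section, have a primary outcome of "Efficacy of the herbal extracts in COVID 19 positive patients (in declining viral load: time-point: 5 days and early recovery" and a secondary outcome of "Efficacy of the investigational product in reducing sequela of the disease". Safety covers liver and kidney function and signs of serious allergic reaction. Restoring respiratory health is a secondary objective. Data Analysis states that all data collected will be analysed, including those of patients who drop out or are lost.

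**The concern.** The footnote is a data-capture rule. It says what goes into the record when no measurement was taken. It does not define the available information or how to extrapolate from it. Nowhere does the protocol ask for such entries to be flagged, sourced or kept out of the analysis. The schedule also creates the situation itself, by asking for a physical examination at visits that are, or may be, telephone calls.

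A value inferred from an earlier or expected state can miss a real change in the patient's condition, and it makes follow-up look more complete than it was. A blank can be handled as missing data. An unmarked substitute cannot be told from an observation by whoever later analyses the file. For that reason this is not something a statistical analysis plan can be relied on to repair.

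**Working it through.** The plan gives no figure on this point, so the check is a comparison of sections followed by a count.

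**1. Where an examination is required, and how the visit takes place**

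| Visit | Assessment table | Study Design | Methods and Procedures |
|---|---|---|---|
| Day 5 | examination due | swab for all subjects | clinical |
| Day 15 | examination due | clinical or telephonic | telephonic or clinical |
| Day 30 | examination due | telephonic, bloods drawn off site | telephonic or clinical |

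The two sections agree on day 15 and conflict on day 30. Study Assessments does not settle it: its general statement includes vitals, but its visit-by-visit descriptions list adherence, missed doses, adverse events, the swab and blood, and do not name vitals.

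**2. Size of the exposure**

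Inputs: 3 post-baseline examinations per patient (assessment table); 60 patients (the flow chart's 30 per arm) to 75 (the upper figure in Study Design and after the sample-size table).

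Scheduled sets = 3 × N: 3 × 60 = 180; 3 × 75 = 225.

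If Study Design governs, day 30 is always remote and day 15 may be:
- lower end = 1 × N: 60 of 180, or 75 of 225 (1/3)
- upper end = 2 × N: 120 of 180, or 150 of 225 (2/3)

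If Methods and Procedures governs, neither visit need be remote:
- lower end = 0
- upper end = 2 × N, as above (2/3)

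Methods and Procedures also mentions a possible extension to 150 patients. That scales the counts (3 × 150 = 450 sets, up to 2 × 150 = 300 remote) but not the shares.

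These figures count visits that are or may be remote. They do not count extrapolated values, and they are not a ceiling: the footnote applies to the whole row, so it also covers day 5 and baseline.

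**3. Which data could be touched**

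- Not touched: RT-PCR viral load at day 5, the day-30 immune markers and immunoglobulins, and liver and kidney function. All are laboratory measurements outside the footnote.
- Touched directly: vitals and physical findings, hence safety signs that an examination could detect, such as rash, swelling or breathing difficulty.
- Touched only if vitals or examination are used to judge them: early recovery, sequelae and respiratory health. The protocol states no measure for any of the three, so the link is possible but not shown.

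**The case against.** Extrapolating from available information need not mean guessing. The information could be the patient's own report or hospital records, and Methods and Procedures has patients continuing routine visits at the site, combined with study visits where possible. The case record form is not shown and might mark such entries. Adverse events are asked about separately at each follow-up and have their own row in the table, so safety does not rest on the examination alone. The trial is double-blind, which makes error favouring one arm less likely. It also calls itself exploratory, and its laboratory endpoints lie outside the footnote.

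Most of this stands, and it limits the point. A reader might infer that invented values enter the efficacy data. The protocol does not support that: no named outcome is defined by vitals or examination, and day 5, the viral-load time-point, is the one follow-up that Methods and Procedures fixes as clinical. A reader might also infer that two-thirds of examinations, and every one at day 30, would be extrapolated. That takes the upper end of the range, ignores Methods and Procedures, and equates a remote visit with an extrapolated value. Nor is the harm always beyond repair: if day 30 is telephonic for everyone, those entries could be set aside by visit.

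The objection does not rescue the sentence itself. A patient-reported or chart-derived reading is legitimate if recorded as such, and the protocol does not ask for that. Blinding does not stop a substituted value from masking a change that occurred.

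**Conclusion.** The point holds in a limited form. The protocol requires examinations at visits that may be telephonic, and tells the physician to extrapolate what could not be examined, with no stated flag. Those values would be analysed along with all other collected data. Remote visits make up 1/3 to 2/3 of post-baseline examinations if Study Design governs, and 0 to 2/3 if Methods and Procedures governs. How many values would actually be extrapolated cannot be known from the protocol.

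The exposure is to clinical safety signs and to any use of examination findings for early recovery, sequelae or respiratory health. The laboratory endpoints are not affected. The conclusion assumes that the case record form does not already separate extrapolated from measured values; nothing in the protocol says that it does. The loss is one of data integrity rather than a demonstrated bias between arms, and it is worth correcting before data collection because the correction is nearly free.

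**What to change.** Delete the extrapolation sentence from the notes to the Study Assessment Table and replace it with: *If vitals or physical examination are not performed, record Not Done with the reason; values reported by the patient or obtained remotely are recorded with their source and flagged.* Treat the resulting gaps as missing data.

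Then reconcile the mode of the day-15 and day-30 visits, and the examination cells for those days, across Study Design, Methods and Procedures, Study Assessments and the assessment table. How the day-15 and day-30 cells are resolved is for the sponsor to decide; what matters is that the sections agree.

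The cost is small: one sentence, the affected table cells, matching edits to the visit descriptions, and a not-done and a source field on the case record form if it lacks them. The downside is more visibly missing vitals.
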